### Composition of the data monitoring committee, its role, and reporting structure {21a}

Data monitoring will be carried out by an independent safety monitor who will ensure the compliance with the trial regulatory aspects and will verify data collection. The safety monitor acts as a representative of the study promotor.

### Adverse event reporting and harms {22}

Due to the intervention types, serious adverse events are not expected. Serious adverse events will be reported by the promotor only if they are directly related to the protocol. Each adverse event will be recorded in the CRF by the principal investigator and will be monitored until resolution or stabilization. The principal investigator will evaluate each event and its gravity and will contact the trial promotor.

### Frequency and plans for auditing trial conduct {23}

Investigators accept to comply with the regulatory requirements of the promoter and the competent authority for a research audit. Audit may be carried out at any stage of the trial, from the protocol development to the publication of results and archival of the data used for the study.

### Plans for communicating important protocol amendments to relevant parties (e.g., trial participants, Page 27 of 40 ethical committees) {25}

All protocol modifications must be submitted to and validated by the Local Human Subject Protection Committee before their implementation. When the protocol modification is accepted by the committee, the research assistant ensures that the changes are implemented accordingly.

### Dissemination plans {31a}

All communication of results must receive the prior agreement of the principal investigator and promoter. Montpellier Hospital is the data owner and must be mentioned as the trial promoter. Regardless of magnitude or direction of effect, data will be published in a scientific review. It is expected that the article with primary outcomes results will be published once all data are validated by the Department of Medical Information composed of data manager, statistician, and methodologist. On request, participants will be informed about the trial overall results by the principal investigator.

## Discussion

This randomized controlled trial wants to investigate whether a CBT program can improve aggressivity in children with ADHD and ED. To this aim, the trial compares the effects of two interventions (CBT and TBI) on emotional and behavioral components in children with ADHD and ED. A parent management program is implemented in both groups. Secondary objectives are to examine the intervention impact on the child’s socio-communicative capacities, quality of life, executive function, and overall functioning at the end of the intervention and after 6 months. The last objective is to examine the intervention effects on parental stress, quality of life, and depressive symptoms. This is one of the first studies that evaluate the short- and long-term efficacy of a psychosocial intervention on aggressive behavior in children with ADHD and ED. Most studies tend to assess effectiveness in the short term (i.e., at the end of the intervention or after 3 months). To our knowledge, no study on psychosocial interventions in children with ADHD and ED assessed the effects of such programs after 6 months.

The results from this trial will be useful for the management of children with ADHD and ED, because this type of interventions should allow children to develop emotional and behavioral self-regulation skills by learning techniques to manage anger (relaxation, resolution problems…). Indirectly, it is expected that the program will promote the development of prosocial skills, leading to a more harmonious relationships with peers and family. For parents, the trial objective is to improve their educative strategies, and also the quality of family life and relations.

The primary limitation of the trial is the lack of tools to detect the intervention effects on ED in children with ADHD. Indeed, most of the available tools for ED evaluation (Bunford, Evans, & Wymbs, 2015), such as physiological, observational, and neuropsychological measures, do not take into account the specificities of subjects with ADHD [32]. Therefore, the subscale “Aggressive behavior” of the CBCL-DP was selected as the primary outcome, because it allows evaluating the degree of severity of aggression in children and adolescents [5] and is a good ED marker.

ADHD represents a public health problem, because it has a significant impact on the children and their family’s daily life and represents an economic burden [48]. Developing effective early psychosocial treatment options for children with ADHD and ED is particularly important in order to prevent developmental trajectories with poor prognosis (social difficulties, comorbidities, persistence of ADHD symptoms), and possibly to limit the need of pharmacological treatments.

## Trial status

Protocol version: August 8, 2018 Version n°3.

Date of recruitment: June, 2017

End of recruitment: September, 2020

The article was submitted after the end of recruitment and not at the beginning: with the co-authors, we favored the implementation of research (doctors' information for recruitment, animation of groups) as well as the writing of a background article that has been published. In addition, due to the pandemic, several participants of the last group dropped out of the study. We had the agreements of the methodologist and the research assistant to extend recruitments and continue the study with another session. Research is currently underway as patients are still participating in groups.

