### Sample size {14}

As ED in children with ADHD has been only recently studied, it is difficult to find literature data for calculating the number of subjects required (particularly for assessing the changes in the “Aggressive behaviors,” “Anxiety/Depression,” and “Attentional Problems” scores of the CBCL scale).

The study by Masi et al [54]. reported a change in the “Aggressive behavior” score of the CBCL from 68.3 to 65.5 in the context of the non-comparative evaluation of an intervention similar to the one assessed in the present trial. The standard deviation of the score at the baseline was 5.4.

By making the reasonable assumption of a slightly more effective intervention than what reported by Masi et al [55]., a CBCL score of 65 in the intervention group and 69 in the control group, with a common standard deviation of 5.5, can be expected at month 6 post-intervention. To highlight such a difference with a power of 80% and an alpha risk of 5%, 31 subjects per group need to be included. By increasing this number by 10% to take into account participants lost to follow-up, the total number of subjects to be included in the study is 68 (34 per group).

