## Assignment of interventions: allocation

### Sequence generation {16a}

After verification of the eligibility criteria, family’s information, and consent signature, each participant will be randomized. Intervention allocation will be done using a computer-based random number generator. Randomization will be performed as soon as the number of participants is reached to start a session (one CBT group and one TBI group) with a 1:1 ratio.

Randomization will be stratified by school level (primary vs middle school) and severity of psychopathological disorders using the CBCL A-A-A score. Children will be divided in groups according to their school level (< 11 years, and 11–13 years of age).

The investigator in charge of the study assessments is blinded to the group allocation.

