## Statistical methods

### Statistical methods for the primary and secondary outcomes {20a}

An intention-to-treat approach will be used to analyze the primary and secondary data from the trial. Participants will be analyzed in their randomization arm and cannot change group during the study.

The primary outcome measure is the changes of the “Aggressive behavior” sub-score between T1 (baseline) and T3 (month 6 post-intervention). A *Z* test will be used to compare the changes of the primary (between T1 and T3) and secondary outcomes (between T1 and T2/T3) in the CBT group and TBI group. In the case of group non-comparability, a multivariate model by linear regression could be carried out to take into account the potential confounding bias.

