### Methods in analysis to handle protocol non-adherence and any statistical methods to handle missing data {20c}

Analysis of the primary and secondary outcomes will be carried out per protocol for all families who participated in two thirds of the intervention.

For missing data, under the hypothesis of a Missing at Random (MAR) or Missing Completely at Random (MCAR) mechanism, an imputation method using the Markov chain Monte-Carlo method will be used with 15 imputation cycles. The analysis will be performed independently for each complete database and the results will be taken into account for estimating the final parameters and their standard deviations.

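### Children are randomised in waves, but the fixed Z test ignores wave, so shifts shared by both arms of a wave stay in its error term; bias from the pandemic-period dropout is possible but not shown.

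*Protocol article*

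**What the plan says.** **Randomisation.** Sequence generation {16a} states: "Randomization will be performed as soon as the number of participants is reached to start a session (one CBT group and one TBI group"), at a 1:1 ratio. Each wave is thus a randomisation block holding both arms. The named stratification factors are school level and CBCL A-A-A severity; wave is not among them.

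**Analysis.** Statistical methods {20a} fixes a Z test that "will be used to compare the changes of the primary (between T1 and T3) and secondary outcomes". Linear regression is mentioned there and under Methods for additional analyses {20b}, but only if the groups turn out not to be comparable.

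**Missing data.** Section {20c} says that "under the hypothesis of a Missing at Random (MAR) or Missing Completely at Random (MCAR) mechanism, an imputation method" by Markov chain Monte Carlo will be used, with 15 imputations. It does not list the variables in the imputation model.

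**Conduct.** Trial status gives June 2017 and September 2020 as the start and end of recruitment. It says that "due to the pandemic, several participants of the last group dropped out of the study" and that recruitment was extended for another session. It gives no count, no split by arm and no losses for other groups.

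**Sample size {14}.** The plan assumes "a CBCL score of 65 in the intervention group and 69 in the control group, with a common standard deviation of 5.5", and concludes that "31 subjects per group need to be included".

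**The concern.** When each wave contributes equal numbers to both arms, anything that moves a whole wave's change scores cancels from the arm difference. A test that pools children across waves still counts that movement as random error. Its standard error is then larger than the design warrants, and power is lost.

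Wave shifts are plausible here. Recruitment spans more than three years and ends in the pandemic. According to the article's description of the primary outcome, the CBCL covers the past 6 months, so the T3 score summarises the family's circumstances over follow-up. The section on other measures says that life events could affect the results.

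The fallback regression does not solve this. It depends on observed imbalance, and wave is balanced by arm at randomisation.

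Dropout raises a second, conditional issue. If a wave with different changes loses more children from one arm, the balance is broken and a wave-blind comparison mixes calendar period with treatment.

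**Working it through.** **1. The plan's own figure.** Inputs from Sample size {14}: difference 69 − 65 = 4, SD 5.5, power 80%, alpha 5% (two-sided reproduces the figure).
- Normal formula: 2 × [5.5 × (1.96 + 0.84) / 4]² = 29.7, so 30 per arm.
- t-based: power is 79.1% at 30 and 80.4% at 31, so 31 per arm.
- Losses: 31 × 1.10 = 34.1, taken as 34 per arm, 68 in total.

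The sample size reproduces and is not in question.

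**2. Ignoring wave, closed form.** Assumptions: no losses beyond the planned 31 per arm, total SD of the change score 5.5 (the protocol gives this SD for the T3 score), and a share ρ of that variance lying between waves. No value of ρ is in the documents.
- Standard error the Z test reports: 5.5 × √(2/31) = 1.397.
- True standard error: 1.397 × √(1 − ρ).
- Error rate: 2 × [1 − Φ(1.96 / √(1 − ρ))].
- Power ignoring wave: Φ[(4 − 1.96 × 1.397) / true SE]. Power with wave modelled: Φ[4 / true SE − 1.96].

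| ρ | Z-test error rate | Power, wave ignored | Power, wave modelled |
|---|---|---|---|
| 5% | 4.4% | 82.3% | 83.6% |
| 10% | 3.9% | 82.9% | 85.5% |
| 20% | 2.8% | 84.4% | 89.3% |

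**3. Ignoring wave, simulation.** Assumptions: six waves of 12 (6 per arm, so 72 children, slightly more than 68), SD 5.5 within wave, true difference 4, no dropout, no correlation within therapy groups; 20,000 trials per setting. Here the wave shift adds to the total variance, so power falls; in step 2 the total was held at 5.5.

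| Setting | Z-test error rate | Z-test power | Wave model |
|---|---|---|---|
| No wave shift | 5.3% | about 87% | 4.9%, 86% |
| One wave shifted 4 to 6 points | 4.6% to 3.7% | 85% to 83% | about 5%, 86% |
| Two waves shifted 4 to 6 points | 4.2% to 3.3% | 85% to 81% | about 5%, 86% |

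**4. Uneven losses.** Assumptions: 34 per arm, 6 per arm in the affected wave, a shift in that wave's change scores, and d children lost per arm. Among completers,

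bias = shift × [(6 − d_CBT)/(34 − d_CBT) − (6 − d_TBI)/(34 − d_TBI)].

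| Losses CBT vs TBI | Shift 2 | Shift 4 | Shift 5.5 |
|---|---|---|---|
| Equal (3 vs 3) | 0 | 0 | 0 |
| 3 vs 1 | 0.11 | 0.22 | 0.30 |
| 4 vs 1 | 0.17 | 0.34 | 0.47 |
| 5 vs 1 | 0.23 | 0.47 | 0.64 |

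These are absolute sizes; the sign depends on which arm loses more and which way the wave moves. The extreme corner, 5 vs 0 with a 6-point shift, is 6 × (1/29 − 6/34) = −0.85, about 21% of the planned 4 points. In 4,000 simulated null trials per setting (five waves, completers only), the Z test's error rate was 6.1% (4 vs 1, shift 4) and 6.9% (5 vs 1, shift 5.5), against 5.2% and 4.7% with wave in the model. With 3 vs 3 both were 5.1%.

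**5. Correlation within therapy groups.** Adding an assumed intraclass correlation of 0.05 to the step 3 layout with one wave shifted 4 to 6 points gives error rates of about 6% to 8% for the Z test and about 8% for the wave model. At 0.10 they are about 9% to 10% and about 12%.

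**The case against.** Much of the case on the other side stands.

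- **Dropout concentrated in one wave.** A reader might infer from Trial status that losses were concentrated in the last group and that missingness depends on wave. The text says only that several of that group dropped out; there is nothing to compare it with. Nor does dropout mean a missing T3 score: section {18b} has families who stop asked whether they will complete the final questionnaires, and allows telephone completion.
- **A biased result.** A reader might infer that the pandemic has biased the comparison. That needs uneven losses by arm and a wave whose changes differ, and neither is documented. Step 4 also drops the lost children, whereas the plan imputes them, and T1 and T2 scores may carry part of a wave shift. Stable level differences between waves cancel from a change score, so the shifts assumed must be shifts in change.
- **A faulty imputation.** A reader might infer that the imputation omits wave. Section {20c} lists no predictors at all, which an article commonly leaves to the full plan. Naming MCAR beside MAR alters no calculation, since MCAR is a special case and the method is the same under both.
- **An error rate below 5%.** This holds only without therapy-group correlation. Step 5 shows that a modest correlation reverses the direction, and that a wave term alone then gives a higher error rate than the Z test.
- **Small size.** In step 3 the Z test's power stays above the planned 80% in every setting.

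What the objection does not remove is that the test is fixed in the text, has no term for the randomisation block, and has a fallback that would not reliably supply one.

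**Conclusion.** The concern holds in a limited form. The stated Z test does not analyse the trial as it was randomised. If waves differ and children within a therapy group are uncorrelated, it is somewhat conservative: an error rate of about 3% to 4.6% and power of 81% to 85%, against 5% and 86% with wave modelled, for the assumed six waves of 12, SD 5.5 and shifts of 4 to 6 points in one or two waves. The number and size of waves and the size of any shift are not in the documents.

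Bias is a possibility and has not been shown. It is zero with equal losses by arm, about 0.1 to 0.6 points for the uneven splits up to 5 vs 1 and shifts of 2 to 5.5 points, and 0.85 points in the 5 vs 0 corner. The documents support neither a statement that the result is biased nor one that the imputation is wrong. The conservative error rate is also not the net rate, because therapy-group correlation acts on the same test in the opposite direction.

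**What to change.** - In Statistical methods {20a}, replace the Z test with a pre-specified linear model for the primary and secondary outcomes that includes randomisation wave as a fixed block factor, whatever the baseline comparison shows.
- Handle correlation within therapy groups in the same model. A wave term alone shrinks the standard error without addressing it.
- In section {20c}, state that wave and arm enter the imputation model, so that it matches the analysis model.
- Report losses by wave and arm, which will show whether the conditions for bias arose.

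**Cost.** This is a change of analysis wording. According to Interim analyses {21b}, analysis waits until all visits are done, and Trial status says that patients were still in groups, so it could be specified beforehand. The wave term costs a few degrees of freedom (five if there are six waves), which is under about 1 point of power if waves do not differ. Allowing for therapy-group correlation costs more: with six waves there are 12 therapy groups, leaving 12 − 6 − 1 = 5 degrees of freedom between groups for the arm comparison. That cost belongs to the clustering and would be due with or without a wave term.

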## Abbreviations

ADHD: Attention deficit hyperactivity disorder
CBT: Cognitive behavioral therapy
CRF: Case report from
ED: Emotional dysregulation
TBI: Theater-based intervention
